
3 ASSESSMENT SCHEDULE

| Study phase                               | Phase I                              |                      |                         |                         |                         |                          | Phase II                  |                           |                           |                           |                           |                           |                           |                                            |                                             |
|-------------------------------------------|--------------------------------------|----------------------|-------------------------|-------------------------|-------------------------|--------------------------|---------------------------|---------------------------|---------------------------|---------------------------|---------------------------|---------------------------|---------------------------|--------------------------------------------|---------------------------------------------|
|                                           | Screening
≤ 6 weeks
(-42 days) | Baseline
(week 0) | Week
2*
(±7 days) | Week
4*
(±7 days) | Week
8*
(±7 days) | Week
12*
(±7 days) | Week
24*
(±14 days) | Week
36*
(±14 days) | Week
48*
(±14 days) | Week
60*
(±14 days) | Week
72*
(±14 days) | Week
84*
(±14 days) | Week
96*
(±14 days) | Week
108*/ET a
(±14 days) | Week
112 / FU b
(±14 days) |
| Study Procedures                          | Visit 1                              | Visit 2              | Visit 3                 | Visit 4                 | Visit 5                 | Visit 6                  | Visit 7                   | Visit 8                   | Visit 9                   | Visit 10                  | Visit 11                  | Visit 12                  | Visit 13                  | Visit 14                                   | Visit 15                                    |

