| Study drug – administration at study site |                                      | X                    |                         | X                       | X                       | (X)                      |                           |                           |                           |                           |                           |                           |                           |                                            |                                             |
| Study drug issuance                       |                                      |                      |                         |                         |                         | X                        | X                         | X                         | X                         | X                         | X                         | X                         | X                         |                                            |                                             |
| Returned drug account                     |                                      |                      |                         |                         |                         |                          | X                         | X                         | X                         | X                         | X                         | X                         | X                         | X                                          |                                             |

\*Weeks after first Golimumab administration, study visits 3 to 6 have a time window of  $\pm 7$  days, and the study visits 7 to 15 – a time window of  $\pm 14$  days. If a subject has an out of window visit the next visit should occur according to the original schedule based on the date of the baseline visit (Visit 2 / Week 0)

a. ET = early termination visit only for subjects who prematurely discontinue study in the Phase II for any reason; should be performed within 4 weeks of last dose of study drug.

b. FU = Follow-up phone visit, collection of the safety information; to be performed 12 weeks after Week 108/ET visit.

c. Interim history.

d. Heart rate, blood pressure.

e. Former and actual smoking state at baseline, actual smoking status at subsequent visits.

f. Spinal mobility (BASMI), function (BASFI), disease activity (BASDAI, ASDAS, overall pain, night pain, PASS, PhASS), global assessment (patient/physician), overall health status / quality of life (ASAS health index).

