## 6.5 Study Treatment

### 6.5.1 Treatments Administered

Included patients will receive Golimumab 50 mg administered subcutaneously by the study personnel or self-administered during the study visit at baseline (week 0), Week 4, 8 and 12. The following dosages will be self-administered by the patient as SC injections every 4 weeks. In the Phase II, subjects included in the Golimumab-Combined-Arm will receive in addition Celecoxib 400mg per os (2 capsules containing 200 mg each) daily.

If the administration of the study drug Golimumab should not be performed in the opinion of the investigator at the planned date due to AE (e.g. infections or clinically significant laboratory abnormalities), the administration should be possible after resolution of the AE, but not later than 14 days after the scheduled injection date. If Golimumab administration is not possible within this time window, this injection should be skipped and next injection has to be done according to the original schedule. Treatment with Celecoxib could be interrupted if necessary for up to 4 weeks.

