## 7 SAFETY CONSIDERATIONS

### 7.1 Definition and Reporting of Adverse Events

An adverse event (AE) is defined as any new undesirable medical occurrence in a clinical investigation subject / patient having received at least one dose of a study drug; this does not necessarily have to be a causal relationship with the study treatment. An AE can therefore be any unfavourable and unintended sign (including an abnormal laboratory finding, for example), symptom, or disease during the time course of the study.

Such an event can result from use of the drug as stipulated in the trial or labelling, as well as from accidental or intentional overdose, drug abuse, or drug withdrawal. Any worsening of a pre-existing condition or illness is considered an AE. Worsening in severity of a reported AE should be registered as a new AE. Laboratory abnormalities and changes in vital signs are considered to be AE only if they result in discontinuation from the study, needs therapeutic medical intervention and/or if the investigator considers them to be an AE.

Following the subject's written consent to participate in the study, all serious AEs (SAE) should be collected. All other AEs should be collected throughout the treatment period from Week 0 until Week 108 and 4 weeks thereafter in the "Safety-Follow-up Visit" at Week 112.

If AEs occur, the subject should be followed until resolution or stabilization, and reported as serious AEs if the AE becomes serious. This also applies to subjects experiencing AEs that cause interruption or discontinuation of the investigational product, or those experiencing AEs that are present at the end of their participation in the study; such subjects should receive post-treatment follow-up as appropriate. If an on-going AE changes in its severity or in its perceived relationship to study drug, a new AE entry for the event should be completed.

A pre-planned elective surgery/procedure scheduled to occur during the study will not be considered an AE if the surgery/procedure is being performed for a pre-existing condition and no worsening of the pre-existing condition occurred during the study.

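### The visit-window note lets the Week 112 safety contact fall on the day of the Week 108 visit if follow-up is 4 weeks, and cannot be met if follow-up is 12 weeks as footnote b says

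*Protocol*

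**What the plan says.** The note under the schedule in section 3 of the protocol defines the weeks as "Weeks after first Golimumab administration". It says "study visits 3 to 6 have a time window of" ±7 days and "the study visits 7 to 15 – a time window of" ±14 days. After an out-of-window visit, "the next visit should occur according to the original schedule based on the date of the baseline visit". Section 6.1 repeats the rule. Visit 15 is the Week 112 follow-up phone call, and its column heading also shows ±14 days.

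The timing of that call is given in two ways:

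- **4 weeks after Week 108.** The study duration in the synopsis, section 6.1, section 7.2.2 and section 13 say this. Section 7.1 has adverse events collected "from Week 0 until Week 108 and 4 weeks thereafter".
- **12 weeks or 3 months.** Footnote b in section 3 times the call 12 weeks after the Week 108/ET visit. The safety paragraphs of the synopsis and of section 5.2 say 3 months after treatment stops.

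In the run-in, section 6.1 plans safety assessments at Weeks 2, 4 and 8 and four-weekly golimumab. Section 6.5.1 has golimumab given at the baseline, Week 4, Week 8 and Week 12 visits. It allows an injection to be postponed because of an adverse event, "but not later than 14 days after the scheduled injection date".

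**The concern.** Week 108 and Week 112 are 28 days apart and each carries ±14 days from the same baseline anchor, so the two windows meet. The follow-up contact is the only scheduled collection of safety data after Week 108, and the synopsis and section 5.2 tie its purpose to long-term NSAID use. If it can take place on the day of the Week 108 visit, the post-treatment period that the protocol describes is not guaranteed, and its length varies between patients for no clinical reason.

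Footnote b does not settle this within the note, because it places the contact outside the window that the note assigns to Visit 15. Early-termination patients share the follow-up column, and a date counted from baseline has no sensible meaning for them.

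The run-in has a lesser version of the same fault. Visit windows, dosing interval and permitted delay all act on the same injections, and the protocol does not say how they combine.

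**Working it through.** **Inputs.** Baseline is day 0 and the nominal day is 7 × week. The tolerance is 7 days for Visits 3 to 6 and 14 days for Visits 7 to 15 (section 3 note, section 6.1). The last golimumab injection is at Week 104 (sections 6.1 and 6.7), with a permitted delay of 14 days (section 6.5.1).

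**The plan's own figure.** 108 + 4 = 112 weeks, as the synopsis states. Footnote b would give 108 + 12 = 120 weeks.

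**4-week reading.**

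- Week 108: 756 ± 14, days 742 to 770.
- Week 112: 784 ± 14, days 770 to 798.
- Shortest interval: 770 − 770 = 0 days. Longest: 798 − 742 = 56 days. Nominal: 28 days.
- Golimumab: the last injection is nominally on day 7 × 104 = 728, or on day 742 if delayed by 14 days. A contact on day 770 is 770 − 728 = 42 days or 770 − 742 = 28 days later.
- Celecoxib: the protocol names no last day of intake. The 96 weeks of randomised treatment from Week 12 end at Week 108. If celecoxib is taken up to a Week 108 visit on day 770, a contact that day gives 0 days of follow-up.

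**Footnote b reading** (actual Week 108 visit + 84 days).

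| Week 108 visit | Target day of contact | With ±14 days |
|---|---|---|
| day 742 | 826 | 812 to 840 |
| day 756 | 840 | 826 to 854 |
| day 770 | 854 | 840 to 868 |

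None of these ranges overlaps days 770 to 798. A patient with an in-window Week 108 visit cannot satisfy both footnote b and the Week 112 window.

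**Early termination.** A patient whose ET visit falls at Week 60 would wait 112 − 60 = 52 weeks for a baseline-anchored Week 112. Under footnote b the wait is 12 weeks.

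**How widespread.** Of the 12 consecutive pairs among Visits 3 to 15, two touch: Weeks 108/112 and Weeks 2/4. The other gaps between windows are 14 days (Weeks 4/8 and 8/12), 63 days (Weeks 12/24) and 56 days (every pair from Weeks 24/36 to Weeks 96/108).

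**Run-in.**

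- Week 2: 14 ± 7, days 7 to 21. Week 4: 28 ± 7, days 21 to 35. They share day 21.
- Week 4 to Week 8 injections on visit windows alone: from 49 − 35 = 14 to 63 − 21 = 42 days, against 28.
- Week 8 injection delayed by 14 days (56 + 14 = day 70) and Week 12 visit 7 days early (84 − 7 = day 77): 77 − 70 = 7 days.

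**The case against.** The strongest reply is that footnote b already ties the contact to the actual Week 108/ET visit. The Week 112/FU heading also lacks the asterisk that leads to the window note from the other on-treatment week columns. A patient who follows footnote b is contacted at least 84 − 14 = 70 days after the Week 108 visit, never on the same day. This stands, and it limits the 0-to-56-day range to the 4-week reading. It does not clear the note, which names Visit 15 expressly in sections 3 and 6.1. The Week 112 heading carries ±14 days as well.

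Other points that stand:

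- Each same-day case needs one visit on its last permitted day and the next on its first.
- Section 7.2.2 asks for serious events for at least 30 days after the last drug in early discontinuers, and for possibly related ones after that. Both arms share the same windows, and no bias between arms is shown.
- Week 4 is itself a safety visit with examination and blood tests, so the second injection is not without a safety check even when Weeks 2 and 4 coincide.
- The 7-day injection interval is a constructed extreme. It joins an exception for adverse events to an early visit, and the ±7 days are stated for visits, not injections.

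A reader might infer that every pair of neighbouring windows touches, that any fully compliant patient could have no safety follow-up at all, or that follow-up after golimumab could vanish. The documents do not support these. Only two pairs touch, compliance with a same-day contact depends on the 4-week reading, and golimumab follow-up stays at 28 days or more.

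**Conclusion.** The point holds in limited form: the window note does not work on either reading of the follow-up length. On 4 weeks it permits a contact 0 to 56 days after the Week 108 visit in place of 28. On 12 weeks it conflicts with footnote b for every patient who has an in-window Week 108 visit. Deciding between the two lengths does not repair it alone, because keeping 4 weeks leaves the shared day 770 in place.

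The loss of follow-up after celecoxib rests on the assumption that intake continues to the Week 108 visit. Sample size, power and significance level are unaffected. The note should be corrected, since the safety follow-up depends on it and the change is small. The shared day 21 and the unaligned run-in injection rules are a minor point of reconciliation.

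**What to change.** Reconcile the window note in sections 3 and 6.1, the Week 112 column and footnote b, together with the passages that give 4 weeks and those that give 12 weeks or 3 months. Count Visit 15 from the actual date of the Week 108/ET visit, for completers and early-termination patients alike. Give it a window that cannot shorten whichever follow-up length the protocol keeps. State the last day of celecoxib intake so that the follow-up after it can be read from the schedule.

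For the run-in, reconcile the ±7-day visit windows, the four-weekly dosing text and the 14-day delay in section 6.5.1, and say how the Week 2 and Week 4 visits relate when both fall on day 21. The choice of rule is the sponsor's.

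The cost is a few reworded sentences and a later last contact for some patients. With a Week 108 visit on day 770, the 4-week reading puts the contact on day 770 + 28 = 798 in place of the nominal 784, which is 14 days later. The 12-week reading puts it on day 854, which is 854 − 798 = 56 days beyond the latest day that the Week 112 window now allows. Any tolerance after the target date adds to these figures, and database lock would move with the last contact.

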## 4 INTRODUCTION

### 4.1 Prevalence and Clinical Manifestations of Ankylosing Spondylitis

Ankylosing spondylitis (AS) is a chronic inflammatory disease of unknown aetiology with primary involvement of the axial skeleton (sacroiliac joint [SIJ] and spine), starting in most of the cases in subjects under 45 years of age and with a strong association with the MHC class I antigen HLA-B27, which is positive in 90-95% of the patients. AS patients can develop peripheral joint and entheses manifestations, as well as extra-articular manifestations such as anterior uveitis, psoriasis and inflammatory bowel disease. The prevalence of AS is estimated to be between 0.1 and 1.4%. The disease is characterized by the presence of active inflammation in the SIJ and the spine, which manifests as pain and stiffness, and by excessive new bone formation (leading to the development of syndesmophytes and ankylosis in the same areas). This will produce in up to 40% of the patients a significant functional impairment and may occur with a close relationship between the grade of impairment and the duration of the disease. At the same time, the disease has a relevant socio-economic impact due to disability and chronic therapies including biological drugs, generating high costs. Reduction of clinical burden and prevention of disability can probably be best achieved by early and adequate treatment targeting for both inflammation and new bone formation.

### 4.2 Current Treatment of Ankylosing Spondylitis

According to the ASAS/EULAR recommendations, the first-line therapy for patients with AS are NSAIDs, including selective COX-2 antagonists, along with education and continuous exercise/physiotherapy. Therapy with conventional DMARDs such as methotrexate, leflunomide, and sulfasalazine may have some beneficial effect in patients with peripheral joint involvement, but in general are not effective for the treatment of axial involvement. For those patients who had a poor response to NSAIDs, contraindications or intolerance for NSAIDs, the only effective treatment currently available is the anti-TNF therapy; very recently secukinumab, a monoclonal antibody against interleukin(IL)-17, has been approved in the EU for the treatment of active AS based on the positive results of two phase III studies.

### 4.3 Evidence for disease modification in Ankylosing Spondylitis

#### 4.3.1 NSAIDs

There is some evidence that NSAIDs, in particular Celecoxib, might possess not only a symptomatic efficacy but also disease modifying properties in AS, retarding the progression of structural damage (syndesmophytes and ankylosis) in the spine if taken continuously. That might be explained by a direct inhibitory effect on osteoblast genesis and activity. This effect was especially evident in AS patients with elevated CRP, which is also considered a risk factor for radiographic spinal progression in AS. The data from the GESPIC study (a non-interventional observational cohort) showed a similar protective effect against radiographic spinal progression in those patients who had high NSAIDs intake (defined as >50% of the maximum recommended dose) and who were at high risk for radiographic spinal progression (presence of syndesmophytes and/or elevated CRP) at baseline. For diclofenac, however, such effect was not proven in the recently published ENRADAS trial (another study supported by BMBF); this might be explained by the lack of COX-2-selectivity of the drug.

#### 4.3.2 TNF blocker

TNF-blocker agents are used as a second line therapy in patients with AS, if NSAIDs demonstrate no or insufficient clinical effect and have until now the best effect on inflammation and signs and symptoms. Despite good clinical efficacy on inflammatory aspects, TNF-blockers are not able to retard radiographic spinal progression in AS over a period of two or four years.

#### 4.3.3 Combination of NSAIDs and TNF blocker

Many of the patients with AS treated with a TNF-blocker discontinue their NSAIDs due to good symptom control with the anti-TNF agent (including the 5-year GO-RAISE pivotal study on the efficacy of Golimumab in AS). Therefore it has not been possible until now to answer the question of the impact of a combined therapy (TNF blocker and NSAID) on radiographic spinal progression.

It is crucial to clarify whether adding an NSAID (especially a COX-2 selective one) to TNF-blocker treatment is able to stop or reduce radiographic progression, especially in patients at high risk (i.e. with elevated CRP and/or with already present syndesmophytes). The current trial is aimed to determine the effect of the NSAID Celecoxib on radiographic spinal progression in patients treated with TNF-blockers.

If such an effect exists, a benefit of retardation of radiographic spinal progression should be weighed against possible risks related to continuous NSAID therapy. Retardation of radiographic spinal progression shall have a beneficial effect on the long-term functional outcome and spinal mobility in AS patients. In case of a positive result of the trial, an optimized treatment strategy might help to avoid disability related to functional limitations caused by spinal structural damage in AS.

## 5 STUDY OBJECTIVE

The objective of this study is to evaluate the impact of treatment with NSAIDs when added to anti-TNF therapy vs. anti-TNF therapy alone on progression of structural damage in the spine over two years in patients with AS.

### 5.1 Primary Endpoint

- Radiographic spinal progression measured by the change of the modified Stoke Ankylosing Spondylitis Spine Score (mSASSS) over two years of therapy.

### 5.2 Secondary Endpoints

#### Efficacy

- New syndesmophyte formation or progression of existing syndesmophytes after 2 years of treatment.
- Improvement of disease activity, function, axial mobility and quality of life measures at Week 12 and Week 108 in comparison to baseline according to:
  - BASDAI
  - ASDAS
  - CRP and erythrocyte sedimentation rate (ESR)
  - Bath AS Functional Index (BASFI)
  - Bath AS Metrology Index (BASMI) and chest expansion
  - Global assessment (patient/physician), general pain and nocturnal pain on the numeric rating scale (NRS)
  - ASAS Health Index
  - Physician Acceptable Symptom State (PhASS)
  - Patient Acceptable Symptom State (PASS)
  - Percentage of subjects who achieve an ASAS20, ASAS40, ASAS partial remission, BASDAI50 and ASDAS in comparison to baseline;
- Change of soluble and cellular biomarkers of inflammation and bone / cartilage turnover at week 108 in comparison to baseline and their relevance for the prediction of radiographic progression.
- Change of the enteric microbiome profile at week 108 in comparison to baseline.
- Change of osteitis score and scores for the chronic post-inflammatory changes in the spine and sacroiliac joints (SIJ) on magnetic resonance imaging (MRI) by Berlin MRI

scoring method at week 108 in comparison to baseline – for the MRI sub-study patients only.

### Safety

- Number of AE and percentage of patients experienced AE, serious AE and events of interest: infections, malignancies, gastrointestinal events (ulceration, bleeding, perforation, gastric outlet obstruction), thrombotic cardiovascular events (myocardial infarction, stroke, pulmonary artery embolism, peripheral arterial or venous thrombosis), renal impairment (creatinine > 1.8 mg/dl or increase > 0.5 mg/dl vs. Baseline) and hepatic deterioration (AST, ALT, AP or GGT > 5-fold ULN). A safety follow-up visit will be performed 3 months after the discontinuation of the study treatment (either at Week 108 or last study visit in case of early discontinuation) in order to address possible long-term safety issues with special regard to continuous use of NSAIDs.

6 INVESTIGATIONAL PLAN

6.1 Study Design

The study duration includes two phases (Figure 1):

[figure not shown]

- **Phase I (Run-in Phase):** It includes a screening period of ≤6 weeks followed by a 12-week period where all patients receive treatment with Golimumab 50 mg SC every 4 weeks.

**Screening:** Patients will be assessed for study eligibility and will undergo procedures outlined in the visit schedule. During this period a standard chemoprophylaxis of tuberculosis might be initiated if appropriate prior to the first injection of Golimumab. Subjects, who were initially regarded as screen-failures for the study, may be permitted to rescreen once following signing re-consent and require a repeat of the screening procedures.

Baseline: eligibility assessment and start of Golimumab 50 mg SC treatment.

Visits Week 2, 4 and 8: safety assessment according to the recommendations for anti-TNF treatment.

- **Phase II (Core Phase):** it is composed by a 96-week controlled treatment period and a safety follow-up visit at week 112.

Visit at Week 12: assessment of clinical response (achievement of at least 2 absolute points on a scale from 0-10) after 12 weeks of TNF-Blocker treatment in the phase I. Only patients who achieve a good clinical response will be included and randomized 1:1 to receive Golimumab 50mg SC every 4 weeks alone or in combination with Celecoxib 400mg per os daily.

Visits Week 24, 36, 48, 60, 72, 84, and 96: safety assessment according to the current recommendations for anti-TNF therapy (every 3 months); clinical disease activity assessment.

Visit at Week 108 or Early Termination: After the last Golimumab injection at Week 104 or in case of early termination (ET, only in patients who were randomised for further therapy at week 12 of the study).assessment of the primary (radiographic progression) and secondary end-points including safety assessment. A second set of X-rays of the spine and a second MRI of spine and sacroiliac joints (for patients participating in the MRI sub-study) are only to be taken, if the patient reached at least the Week 84 time point. There will be a follow-up period of 4 weeks with a safety follow-up visit (phone call) for the collection of additional safety information.

Visit at Week 112 / Follow-up (FU):

- Visit time windows: Study visits from 3 to 6 will have a time window of  $\pm 7$  days, and the study visits 7 to 15 – a time window of  $\pm 14$  days. If a subject has an out of window visit the next visit should occur according to the original schedule based on the date of the baseline visit (Visit 2 / Week 0).

